**Methods:**

Participants will be healthy individuals across a wide range of ages (6 to 35 years), from two study sites. Participants will undergo pre-exposure and conditioning followed by both a short-term and long-term test of learning, all in a novel virtual reality environment. The unconditioned stimulus will be a brief pressurized puff of air to a maxillary anterior tooth. Pre-exposure dose (low vs. high) and pre-exposure novelty (element stimulus vs. compound stimuli) will be between-subject factors, with stimulus type (pre-exposed to-be conditioned stimulus, a non-pre-exposed conditioned stimulus, and an unpaired control stimulus) and trial as within-subject factors. Pain sensitivity will be measured through self-report and a cold pressor test. It is hypothesized that a larger dose of pre-exposure and compound pre-exposure will potentiate the engagement of the target mechanisms and thereby result in greater latent inhibition in the form of reduced fear learning. Further, it is hypothesized that larger effects will be observed in participants with greater baseline pain sensitivity.

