**Discussion:**

The proposed study will test whether pre-exposure dose and compound stimulus presentation change expected relevance and attention to the pre-exposed stimulus, and thereby enhance latent inhibition of dental fear. If found, the results will add to our theoretical understanding of the latent inhibition of dental fear and inform future interventions for dental phobia prevention.

Research suggests the prevalence of dental anxiety in the United States for adults is approximately 15%, with estimates for youth ranging between 5% and 20% [1–3]. Dental anxiety remains a substantial barrier to recommended oral health care; it is associated with fewer regular dental visits [4, 5], avoidance of dentist advocated treatment [6], and a greater likelihood of missing, diseased, and filled teeth [7]. Poor oral health, which is increased by dental fear and anxiety, has been linked with adverse health consequences beyond the oral cavity, such as heart disease, stroke, and diabetes [8, 9]. Dental anxiety disproportionately affects marginalized individuals in the United States, including Hispanic and African American populations [10, 11].

Consistent with the broader experimental literature on fear and anxiety, direct associative conditioning appears central to the probability of developing dental fear [2]. For example, studies [12–14] report that dental anxiety is higher for individuals who underwent distressing and painful dental experiences early in their dental history. Townend et al. [15] similarly found that youth who were diagnosed with dental anxiety had experienced more early traumatic dental office visits than youth not diagnosed with dental anxiety.

Naturalistic studies suggest pre-exposure to dental stimuli and contexts prior to direct conditioning can impair the development of dental fear. For example, in studies by Davey [12] and De Jongh et al. [13], the experience of non-fearful dental events prior to potentially fearful or distressing dental events, was related to a lower likelihood of dental anxiety. These findings are consistent with research on the learning phenomenon of latent inhibition (LI). LI occurs when previous passive exposure to a stimulus impairs one’s ability of acquiring or expressing a new association with that stimulus [16]. For example, presenting a stimulus alone prior to conditioning trials in which it is paired with a painful shock reduces learning from the conditioning trials [17].

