### Experimental design

The study will use a mixed design, with two within-subject independent variables and two between-subjects independent variables, and one measured continuous moderator variable. One within-subjects variable is stimulus type [stimulus type: pre-exposed to-be conditioned stimulus (CS^+^ _P_), non-pre-exposed to-be conditioned stimulus (CS^+^ _NP_), and an unpaired control stimulus (CS^−^)]. The second within-subjects variable is time [trial number]. One of the two-level between-subjects independent variables is pre-exposure dose [12 trials vs. 24 trials]. The second two-level between-subjects independent variable is pre-exposure novelty [single stimulus vs. compound stimuli]. Participants will be randomly assigned to one of the four between-subject conditions using the randomization feature in the software Research Electronic Data Capture (REDCap; 31, 32). Randomization will be done in session to obtain allocation concealment [33]. The continuous moderator variables are two individual-difference measures of pain sensitivity.

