### Procedures

Participants will experience the virtual reality “game” seamlessly each visit however, the task has four discrete phases: pre-exposure, conditioning, and learning recall phases, all occurring in Visit 1, and a learning retention phase, which occurs in Visit 2. Next, we describe the four phases, explaining the trials in each phase.

Trials in the first phase, the *pre-exposure phase*, will begin with a minimum of six seconds in which the participant is free to navigate around the planet surface to collect fuel concealed in the landscape. Following the initial trial segment, the CS^+^ _P_ is automatically presented, accompanied by a fuel canister, at the first opportunity. The CS^+^ _P_ will be an alien stimulus that displays small vertical movements and associated individualized noises. The CS^+^ _P_ and the fuel canister will appear at a fixed distance from the participant and will be present for the remaining six seconds of the trial. Thus, each trial consists of a six second segment without the CS^+^ _P_, followed by a six second segment with the CS^+^ _P_. During pre-exposure, the CS^+^ _P_ is never accompanied by the UCS.

It is during the *pre-exposure phase* that the two between-subject independent variables are manipulated. First, the number of pre-exposure trials constitute the *pre-exposure dose* independent variable and will be either 12 trials (low dose) or 24 trials (high dose), based on random assignment. Second, for participants in the *single stimulus pre-exposure type condition*, the CS^+^ _P_ will always present in the environment without another alien stimulus. For participants in the *compound stimulus pre-exposure type condition*, a second novel alien stimulus will be immediately adjacent to the CS^+^ _P_ with the presentation period identical to that of the CS^+^ _P_ on the second half of the pre-exposure trials: the final 6 trials for those in the low dose condition, and the final 12 trials for those in the high dose condition.

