### Statistical analysis plan

SPSS software will be used to address Hypotheses 1a, 2a, and 3 described below. Mplus software will be used to address the remaining hypotheses. Note that throughout the analyses, an interaction between the two between-subjects factors is not of primary interest [25]. Rather, we anticipate that a particular combination of the groups, or the focal group, (i.e., high dose and compound condition) will have more favorable responses than each of the other groups. Consequently, we treat these between-subjects factors as one factor with four groups. Note that representing the four cells of the between-subjects factors in this way yields the same fit as a full between-subjects factorial model and readily enables us to assess the comparisons between the focal and other groups.

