#### Hypothesis

1b: A larger dose of pre-exposure, compared to a smaller dose, will strengthen the LI of conditioned fear acquisition, recall, and retention. Hypothesis 2b: Compared to pre-exposure with only the target stimulus, compound pre-exposure will strengthen the LI of conditioned fear acquisition, recall, and retention.

To assess hypotheses 1b and 2b, mediation analysis will be conducted to estimate direct, indirect, and total effects associated with the pre-exposure groups on the distal outcomes of conditioned fear acquisition, recall, and retention. Figure 1 shows the conceptual model that will be estimated for each distal outcome. In the parallel mediation model shown in Fig. 1, the pre-exposure groups are hypothesized to impact the mediators (expected relevance and attention), which in turn are hypothesized to affect a given fear outcome. Note that there are no within-subjects variables in this path model as the scores for the mediating variables will be obtained from the first trial of the conditioning phase, where stimulus group differences are expected to be strongest, and scores from a given distal outcome will be computed as the average of the scores across specific trials in the recall and then retention phase. Note that if the pre-exposure variable was found to interact with stimulus type in hypotheses 1a or 2a, then this model will be estimated separately for each stimulus type to assess if mediation is present for each stimulus.

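### Hypotheses 1b and 2b claim stronger latent inhibition, but no stated analysis of a fear outcome contrasts the pre-exposed with the non-pre-exposed conditioned stimulus

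*Protocol article*

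**What the plan says.** The introductory text defines the phenomenon: "LI occurs when previous passive exposure to a stimulus impairs one’s ability of acquiring or expressing a new association with that stimulus". Hypothesis 1b is that "A larger dose of pre-exposure, compared to a smaller dose, will strengthen the LI of conditioned fear acquisition, recall, and retention", and Hypothesis 2b says the same of compound pre-exposure.

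Under Experimental design, "One within-subjects variable is stimulus type", with three levels: CS+P, CS+NP and the unpaired control CS−. The between-subject factors are dose and novelty. Under Procedures, the number of pre-exposure trials "will be either 12 trials (low dose) or 24 trials (high dose), based on random assignment". Every randomised group is therefore pre-exposed to CS+P. The Statistical analysis plan merges the two factors: "Consequently, we treat these between-subjects factors as one factor with four groups".

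For 1b and 2b the article gives a parallel mediation model: group, then expected relevance and attention at the first conditioning trial, then a fear score averaged over certain recall or retention trials. It adds: "Note that there are no within-subjects variables in this path model". Stimulus type returns only if it interacted with group in the analyses for 1a or 2a; "then this model will be estimated separately for each stimulus type to assess if mediation is present for each stimulus".

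**The concern.** LI is a comparative quantity: learning about a stimulus met before, against learning about one not met before. No group goes without pre-exposure, so CS+NP is the only conditioned stimulus in the study that can serve as the comparator. A claim that LI is stronger in one group than another is a claim about a group difference in the gap between CS+NP and CS+P, that is, a group × stimulus interaction on fear.

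No such test is stated for any fear indicator. Three consequences follow.

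- The default model does not name its stimulus, so its total and indirect effects have no fixed meaning.
- Whether stimulus is considered at all depends on a significance test on other variables (the mediators). A missed mediator interaction would close the route to a stimulus-specific fear analysis.
- Even in the per-stimulus branch, separate CS+P and CS+NP estimates are produced with no test of their difference.

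The trial could then report strengthened LI when fear fell equally to all stimuli, or miss a real CS+P-specific effect.

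**Working it through.** **1. Where group × stimulus is tested (Statistical analysis plan).**

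| Analysis | Dependent variable | Stimulus in model? | CS+P vs CS+NP by group? |
|---|---|---|---|
| 1a/2a, pre-exposure phase | expected relevance; attention | no (only CS+P is shown) | no |
| 1a/2a, conditioning phase | expected relevance; attention | yes | yes, on mediators |
| 1b/2b, default | fear score | no; stimulus not named | no |
| 1b/2b, after a mediator interaction | fear score | one model per stimulus | no test between models |

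The contrast is specified for the mediators and for no fear outcome. This result needs no numerical assumption.

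**2. Time in task before conditioning.** Procedures gives each pre-exposure trial at least 6 s of free navigation plus 6 s with the stimulus.

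- Low dose: 12 × 12 s = 144 s at minimum.
- High dose: 24 × 12 s = 288 s at minimum.

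High-dose participants are longer in the headset and mouthpiece before conditioning, so a general effect on fear is possible for the dose comparison.

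**3. Size, by illustration.** From the article: N = 180 in four groups, or 180/4 = 45 per group if equal (assumed). Also assumed, not in the article: SD 1 for each stimulus, a common between-stimulus correlation ρ of 0.3 to 0.7, a 0.5 SD effect, and two-sided alpha 0.05.

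For an effect on CS+P only, the standardised effect is multiplied by:

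- mean of three stimuli: (1/3)/√((1+2ρ)/3) = 0.456, 0.408, 0.373 at ρ = 0.3, 0.5, 0.7. So 0.5 SD becomes 0.23, 0.20, 0.19 SD;
- CS+NP minus CS+P: 1/√(2(1−ρ)) = 0.845, 1.000, 1.291.

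Check for CS+P alone by normal approximation: Φ(0.5 × √(45/2) − 1.96) = Φ(0.41) = 0.66. Simulation (20,000 runs, two-sample t-tests on the total effect, 45 vs 45) gave 0.65. Proportion of runs significant:

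| Truth | ρ | CS+P alone | Mean of three | Difference |
|---|---|---|---|---|
| 0.5 SD on CS+P only | 0.3 | 0.65 | 0.18 | 0.51 |
| | 0.5 | 0.65 | 0.16 | 0.65 |
| | 0.7 | 0.65 | 0.14 | 0.86 |
| 0.5 SD on all stimuli, LI unchanged | 0.3 | 0.65 | 0.90 | 0.05 |
| | 0.5 | 0.64 | 0.82 | 0.05 |
| | 0.7 | 0.65 | 0.75 | 0.05 |

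In the last three rows, CS+P is significant and CS+NP is not in 18%, 15% and 12% of runs although LI does not differ. A smaller general effect of 0.3 SD would make CS+P alone significant with probability Φ(0.3 × √(45/2) − 1.96) = Φ(−0.54) = 0.30.

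**The case against.** Randomised groups share the same conditioning phase, and stronger LI does predict less fear to CS+P. The authors expect group differences to be largest for CS+P, so the per-stimulus branch is probably the route they foresee, and its CS+NP model would shed some light on a general effect. This stands. A reader might infer that the plan cannot test 1b and 2b at all, but that goes too far: the CS+P effect is relevant evidence, only not specific to LI.

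Other stronger readings are also unsupported.

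- A reader might infer that the default model pools all three stimuli. The article does not identify the trials that are averaged, and they could be CS+P trials alone. The dilution figures hold only under pooling.
- A reader might infer that the per-stimulus models will be judged by one being significant and another not. The article states no such inference; what it lacks is a test of the difference.
- A reader might take the statement that the path model lacks within-subject variables as proof by itself. It is not, because a model of difference scores would also satisfy it. The evidence is the plan to refit by stimulus type, which implies scores for single stimuli rather than a difference between them.
- A reader might extend the time-in-task argument to 2b. Single and compound groups at the same dose have equal trial numbers, so it applies to dose only.

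An article may leave scoring detail to a fuller document. Here, though, it sets out the model, what the model omits and when it is split by stimulus, so the mismatch with the hypotheses lies in what is stated.

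**Conclusion.** The point holds in this form: as stated, the 1b/2b analysis contains no CS+P versus CS+NP contrast on any fear outcome, leaves the default model's stimulus unnamed, and makes the per-stimulus models conditional on a mediator result. That rests on the text alone. A positive result for CS+P could reflect stronger LI or a general reduction in fear, and the analyses given do not formally separate the two.

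The size is illustrative. It depends on the assumed 0.5 SD effect, the correlations of 0.3 to 0.7, equal groups of 45 and, for dilution to 0.37-0.46 of the effect, on the pooled reading. The illustration concerns total effects; it does not evaluate the indirect effects or their bootstrap tests.

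**What to change.** 1. For each fear indicator and phase, make the test of 1b and 2b the group effect on the within-person difference CS+NP minus CS+P, with each indicator scored so that higher means more fear. For the continuous indicators this is equivalent to the group × stimulus term restricted to these two stimuli. For the yes/no approach indicator, use the difference in the proportion of trials or a group × stimulus term in a model for repeated binary data.
2. Run this test always, whatever the 1a/2a mediator analyses show.
3. Always fit the CS+P and CS+NP path models, name the stimulus that each uses, and present them beside the difference.
4. Using the same CS+NP minus CS+P difference for the mediators is optional. Each mediator comes from a single early trial, so differencing may add noise.

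The cost is wording only, since responses to all three stimuli are already recorded. The statistical downside is that the difference has variance 2(1−ρ) relative to a single stimulus, so it is noisier than CS+P alone when ρ is below 0.5. At 45 vs 45 with an assumed 0.5 SD effect, its power is about 0.51, 0.65 and 0.86 at ρ = 0.3, 0.5 and 0.7, against 0.65 for CS+P alone. That is a reason to keep the CS+P model alongside the contrast, but not to omit the contrast.

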## Methods

### Participants

This is a multisite study, with participants enrolled at universities in south Texas and northwest Ohio. For the United States, the region surrounding the Texas site has a larger than average Hispanic population [30], whereas the region surrounding the Ohio site has a substantial African American population [30]. The sites are therefore expected to provide opportunity to recruit Hispanic and African American participants– populations that are of greater risk for dental anxiety and poor oral health [10, 11].

Community volunteers between the age of 6 and 35 will be recruited using strategies such as a study Facebook page, ads posted in social media, newspapers, email announcements, and flyers at community sites. The sample size of 180 participants was determined by an a priori power analysis. Table 1 provides the inclusion/exclusion eligibility criteria for participation. The study will consist of two in-person visits, scheduled approximately 1 week apart, with participant remuneration of a $50 gift card per visit. The Institutional Review Board of the primary institution approved the research.

**Table 1 Tab1:** Inclusion and exclusion criteria

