#### Fear learning measures

Fear learning will be assessed with subjective, physiological, and behavioral indicators. For the subjective indicator, participants will periodically rate their level of relaxation/anxiety when the CS^+^ _P_, CS^+^ _NP_, and CS^−^ are presented. The subjective fear question will be, “How relaxed do you feel?”, with responses provided on a 10-point scale. Skin conductance responses (SCRs) to the CS^+^ _P_, CS^+^ _NP_, and CS^−^ will serve as a physiological indicator of fear learning. To measure SCRs, we will use Biopac MP160 with a wireless BioNomadix module transmitter (Biopac Systems, California, USA.) and Biopac’s Acknowledge 5.0 software (Biopac Systems, California, USA.). Recordings will be made with two Ag–AgCl electrodermal conductance electrodes with Isotonic gel placed on the middle phalanges of the non-dominant hand pinky and ring fingers. SCRs will be analyzed based on prior work [36]. Finally, two variables will be acquired during the trials to provide behavioral indices of fear learning. The first is the shortest distance between the participant and the CS^+^ _P_, CS^+^ _NP_, and CS^−^, which will be recorded on each trial. Second, we will also record whether or not the participant approached the CS^+^ _P_, CS^+^ _NP_, and CS^−^ and obtained the “fuel cell” they appeared with [29].

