#### Hypothesis

1a: A larger dose of pre-exposure, compared to a smaller dose, will increase engagement of the target mechanisms (expected relevance and attention). Hypothesis 2a: Compared to pre-exposure with only the target stimulus, compound pre-exposure will lead to stronger engagement of the target mechanisms of expected relevance and attention.

For Hypotheses 1a and 2a, changes expected in the candidate mediators should first be observed during the pre-exposure phase. To test these hypotheses during this phase, a two factor repeated measures MANOVA with one-between (pre-exposure group) and one-way within-subjects (trial) factor will be conducted separately for the variables expected relevance and attention. A significant group × trial interaction indicates that mean responses across trials is not the same for each group. If the interaction is present, follow-up analyses will focus on examining the plots of the mean change for each group and testing the degree to which the mean change from first to last trial differs between the groups. For the conditioning phase, a three-way repeated measures MANOVA will be conducted separately for each of the target mechanisms (expected relevance and attention). For these models, pre-exposure groups will serve as the between-subjects factor with stimulus and trial being the within-subject factors, and the analysis model will assess the main effects of each variable, as well as all-two-way and three-way interactions. Follow-up analyses depend on the nature of effects that are present (e.g., type of interactions or main effects). We expect that differences between pre-exposure groups will be greater—particularly at the early trials for stimulus CS^+^ _P_ —than for the other stimulus conditions. As such, follow-up analyses will focus on the degree to which means differ by pre-exposure group and stimulus type for each trial using a Bonferonni-adjusted alpha, as well as examining plots of the mean response by stimulus type and trial for each pre-exposure group.

#### Hypothesis 3

Higher pain sensitivity scores will be associated with increased engagement of the target mechanisms of expected relevance and attention.

To test the third hypothesis, individual differences in pain sensitivity will be included in the above analyses as a moderating variable. This will be done by testing interactions between pre-exposure and pain sensitivity.

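### The mediation model and the by-trial group comparisons leave out a baseline the trial already collects on pre-exposure trials 1-6, at a cost in precision and in bias of the mediator-to-outcome path

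*Protocol article*

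**What the plan says.** **Design (Protocol article, Procedures).** The number of pre-exposure trials "will be either 12 trials (low dose) or 24 trials (high dose), based on random assignment". In the compound groups the second alien appears only on "the final 6 trials for those in the low dose condition, and the final 12 trials for those in the high dose condition", so it starts at trial 7 (low dose) or trial 13 (high dose). No group receives the air puff in this phase: "During pre-exposure, the CS^+^ _P_ is never accompanied by the UCS".

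**Measurement.** Under Hypotheses 1a/2a, expected relevance and attention are analysed across the pre-exposure trials, including a test of change from the first trial to the last. Under Fear learning measures, shortest distance is a variable "which will be recorded on each trial", while the relaxation rating is only periodic.

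**Conditioning-phase model (Hypotheses 1a/2a).** The terms are given as "pre-exposure groups will serve as the between-subjects factor with stimulus and trial being the within-subject factors", with main effects and all interactions. Follow-up compares groups by stimulus type at each trial with a Bonferroni-adjusted alpha.

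**Path model (Hypotheses 1b/2b).** Group acts on expected relevance and attention, and these act on a fear outcome averaged over recall or retention trials. The article's words are: "there are no within-subjects variables in this path model as the scores for the mediating variables will be obtained from the first trial". The trial meant is the opening one of conditioning. The text names no covariate in either model.

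**The concern.** A measure of each person's mediator level, taken before the groups can differ, is the natural covariate for that person's later level. Without it, general rating level, gaze habit and approach tendency stay in the error term of every between-group comparison. Participants are aged 6 to 35, so such differences are plausibly wide, and each mediator score in the path model comes from a single trial.

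The mediation model has a second problem. Group is randomised, but the mediators are not. Someone who rates everything high, or who habitually keeps away, may do so in both mediator and outcome. That shared tendency enters the mediator-to-outcome path, and with it the indirect effect. Bootstrapping handles the non-normal sampling distribution of the product and does nothing about this confounding.

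**Working it through.** **1. Is there a clean baseline?**

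| Group | Trials 1-6 | Trials 7-12 | Trials 13-24 |
|---|---|---|---|
| Low, single | CS+P alone | CS+P alone | none |
| Low, compound | CS+P alone | CS+P + second alien | none |
| High, single | CS+P alone | CS+P alone | CS+P alone |
| High, compound | CS+P alone | CS+P alone | CS+P + second alien |

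The first difference is at trial 7. Only trials 1-6 are common to all four groups.

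**2. Inputs.** The document gives a total of 180 ("The sample size of 180 participants was determined by an a priori power analysis") but no effect size, alpha, power or correlation, so 180 cannot be reproduced. Assumed: 45 per group (180/4), d = 0.5, focal group against one other group, and baseline correlation rho of 0.3 or 0.5. If trials are equally correlated with intraclass correlation (ICC) r, a six-trial mean correlates r / sqrt((1 + 5r)/6) with one later trial: 0.35, 0.46 and 0.65 at r = 0.2, 0.3 and 0.5.

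**3. Group-to-mediator path and by-trial comparisons.** Adjustment multiplies the residual variance by 1 - rho^2, i.e. 0.91 or 0.75. Power comes from the noncentral t with noncentrality [d / sqrt(1 - rho^2)] x sqrt(45/2), on 88 df unadjusted and 87 adjusted. The noncentrality is 2.37 unadjusted, 2.49 at rho 0.3 and 2.74 at rho 0.5.

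| Two-sided alpha | Unadjusted | rho 0.3 | rho 0.5 |
|---|---|---|---|
| 0.05 | 65% | 69% | 77% |
| 0.05/12 | 29% | 33% | 42% |

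The second row stands for the by-trial follow-ups. A family of 12 is assumed from the 12 conditioning trials per stimulus; the article does not define the family.

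**4. Group-by-stimulus contrast.** A person's constant level cancels in the difference CS+P minus CS+NP. With unit trial variance its standard error is sqrt[2(1 - r) x 2/45] = 0.249 at r = 0.3 and 0.211 at r = 0.5. A simulation of 4 x 45 participants (4,000 replicates) gave 0.250 unadjusted and 0.251 adjusted at r = 0.3, and 0.211 and 0.212 at r = 0.5. There is no gain.

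**5. Power for the indirect effect when nothing confounds.** Adjustment also removes mediator variance. With unit residual variances, the standard error of the mediator-to-outcome path rises from 1/sqrt(175) = 0.076 to 1/sqrt(174 x 0.91) = 0.079 at rho 0.3, or to 1/sqrt(174 x 0.75) = 0.088 at rho 0.5. Joint power is approximately the step 3 power times Phi(path/SE - 1.96):

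| rho | Path | Unadjusted | Adjusted |
|---|---|---|---|
| 0.3 | 0.2 | 0.650 x 0.754 = 49% | 0.691 x 0.711 = 49% |
| 0.3 | 0.3 | 0.650 x 0.978 = 64% | 0.691 x 0.965 = 67% |
| 0.5 | 0.2 | 0.650 x 0.754 = 49% | 0.773 x 0.627 = 48% |
| 0.5 | 0.3 | 0.650 x 0.978 = 64% | 0.773 x 0.929 = 72% |

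A joint-significance simulation (1,500 replicates) showed the same pattern at rho 0.5: 49% to 48% for path 0.2, and 66% to 71% for path 0.3.

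**6. Bias when a stable trait drives both.** Assume mediator = trait (variance r) + noise (variance 1 - r), and outcome = 0.7 x trait + 0.3 x mediator + noise. The true path is 0.30.
- Unadjusted expectation: 0.3 + 0.7r = 0.51 at r = 0.3 and 0.65 at r = 0.5.
- Adjusted, with baseline variance v = r + (1 - r)/6: 0.3 + 0.7 x r(v - r)/(v - r^2). At r = 0.3, v = 0.417 and the result is 0.38. At r = 0.5, v = 0.583 and the result is 0.39.

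Most of the bias goes, but not all of it. The 0.7 is an assumption.

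**The case against.** The sentence about having no within-subjects variables means only that there is no repeated factor. A trials 1-6 mean is one value per person, so that sentence does not exclude it. Fig. 1 is not shown, and a covariate list may stand in a fuller plan. This is fair, but the text sets out the terms of both models and places no baseline score in either.

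The case against a large effect mostly stands:
- A reader might infer that the 12-point gain at rho 0.5 (65% to 77%) applies to the tests of Hypotheses 1b/2b. It does not. Those test indirect effects, where step 5 shows anything from no gain to about 8 points.
- A reader might infer that the whole conditioning-phase model loses precision. The contrast that best expresses latent inhibition, group by stimulus, loses none.
- A reader might compute the gain for a 90 against 90 dose or novelty contrast. The plan treats the design as one four-group factor and compares the focal group with each other group, so that contrast does not belong here.
- The correlation is unknown. Trials 1-6 come before any air puff, while fear outcomes come after conditioning, in retention at least 7 days later. A value below 0.3 is possible, and the gain would then be small.
- A baseline is not assured for every measure. Relaxation is rated periodically, and the article does not say that expected relevance is rated on every trial.

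**Conclusion.** The point holds as a worthwhile improvement in two places. First, the group-to-mediator path, the group main effect and the by-trial group comparisons lose precision: about 4 to 12 power points at alpha 0.05 and 4 to 13 at 0.05/12, for rho 0.3 to 0.5, under the assumed 45 per group and d = 0.5. Second, the mediator-to-outcome path, and so the indirect effect, is open to confounding by stable response style. Reducing that bias is the main benefit in the mediation model; extra power there may be slight. How large the bias is depends on a trait effect that the document does not let anyone estimate.

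A reader might also infer that the randomised group comparisons are invalid without adjustment. The documents do not support that: assignment is random, and the unadjusted comparisons are valid, only less precise.

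**What to change.** **Path model (Hypotheses 1b/2b).** Regress each mediator on its own mean over CS+P pre-exposure trials 1-6. Regress each fear outcome on both baseline mediator means, and on its own trials 1-6 mean where that measure is recorded then. Shortest distance qualifies; the relaxation rating qualifies only if it is taken on some of those trials.

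**Conditioning phase.** Use the same mean, centred, as a covariate in the by-trial, by-stimulus group comparisons of expected relevance and attention. For CS+NP and CS- it is still a person-level baseline, though not one for that stimulus.

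**Restriction.** State that only trials 1-6, or those of them on which the measure was taken, may be used, because later pre-exposure trials are affected by group. Fix this before the data are seen, so that covariates are not chosen on results.

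**Cost.** Some analysis wording and one degree of freedom per covariate, with no new data or visits. The gain is small if the correlation is below about 0.3, and the mediator-to-outcome path is slightly less precise (standard error 0.088 against 0.076 at rho 0.5) if there is no confounding to remove.
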